### **10.4 Serious adverse drug reactions**

Adverse drug reactions rated as "serious" in the assessment of seriousness will be considered serious adverse drug reactions and analyzed in the same manner as indicated in subsections 1) and 2) of section 10.1 (adverse events).

### **10.5 Hemorrhagic adverse events**

Hemorrhagic adverse events will be analyzed in the same manner as indicated in subsections 1) and 2) of section 10.1 (adverse events). Incidence will be determined for all hemorrhagic events and for hemorrhage determined to be severe or life-threatening based on the GUSTO bleeding criteria. Incidence will be determined according to system organ class and event type (preferred term) based on terminology conversions using MedDRA/J, and the chi-square test will be used to compare these incidences across groups.

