With regard to the combined effect of aspirin and clopidogrel in IS/TIA patients, results of CARESS (Clopidogrel and Aspirin for Reduction of Emboli in Symptomatic Carotid Stenosis), FASTER (Fast Assessment of Stroke and Transient ischaemic attack to prevent Early Recurrence), CLAIR (Clopidogrel plus aspirin versus aspirin alone for reducing embolisation in patients with acute symptomatic cerebral or carotid artery stenosis), etc., demonstrated the efficacy of combined treatment in patients with IS/TIA at relatively early stage of onset. Efficacy of a short-term combination therapy of aspirin and clopidogrel was also demonstrated in the recent CHANE study (Clopidogrel in High-risk patients with Acute Non-disabling Cerebrovascular Events). However, long-term combined use of aspirin and clopidogrel is not recommended as it increases serious bleeding complications, even though there is no change or even a slight decrease observed in vascular events.

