#### **24.7. Adverse event-related actions**

Existence of therapy (a drug therapy or other treatment) and contents of the therapy conducted for developed adverse events should be recorded.

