### **2.3 Safety evaluation**

The following will be the safety endpoints.

- Adverse events and adverse drug reactions
- Severe or life-threatening hemorrhage (GUSTO criteria)

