#### **GUSTO bleeding criteria**

-Severe or life-threatening hemorrhage:

Intracranial bleeding or bleeding that causes substantial hemodynamic compromise requiring treatment

-Moderate bleeding: Bleeding which requires blood transfusion

-Minor bleeding: Other bleeding, neither requiring transfusion nor causing hemodynamic compromise

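### SAP 10.5 makes no pooled comparison of GUSTO moderate (transfusion-requiring) bleeding, so a rise confined to that grade can be diluted

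*Supplement*

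**What the plan says.** Protocol v1.3 section 9 and SAP 2.3 name one graded bleeding endpoint, severe or life-threatening haemorrhage by GUSTO. SAP 10.5 sets out the pooled analyses: "Incidence will be determined for all hemorrhagic events and for hemorrhage determined to be severe or life-threatening based on the GUSTO bleeding criteria". It also compares haemorrhagic incidences by system organ class and preferred term with chi-square tests.

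The GUSTO list in SAP 10.5, repeated in protocol 29.6, has three grades:

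- The top grade is defined as "Intracranial bleeding or bleeding that causes substantial hemodynamic compromise requiring treatment".
- The middle grade, the one at issue here, is worded "Moderate bleeding: Bleeding which requires blood transfusion".
- The lowest grade takes in every remaining bleed, with no transfusion and no haemodynamic compromise.

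The moderate grade appears in no endpoint, pooled summary or test. SAP 10.5 applies only steps 1) and 2) of SAP 10.1, so the severity distribution in step 3) is not called for there. That distribution in any case uses the daily-activity scale of protocol 24.3, not GUSTO. SAP 10.3 and 10.4 compare serious adverse events and serious reactions overall and by preferred term, again without a GUSTO grade.

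On data capture, protocol 24.7 asks that the "contents of the therapy conducted for developed adverse events should be recorded".

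**The concern.** Bleeding is central to this trial's rationale. Protocol 2.1 says that long-term aspirin plus clopidogrel "is not recommended as it increases serious bleeding complications". The background then presents cilostazol combinations as safer in this respect. For clopidogrel with cilostazol after ischaemic stroke, protocol 14.2 concedes that detailed reports are lacking.

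The planned pooled comparisons are one narrow class, in which few events are likely, and one broad class that includes every minor bleed. A patient transfused for a bleed without substantial haemodynamic compromise is outside the first and counts in the second no more than a patient with a bruise. If DAPT raised this kind of bleeding alone, the severe-only comparison could look balanced and the all-bleeding comparison could bury the difference.

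The choice of rows also affects monitoring. Protocol 11.4.1 sets no formal stopping criterion for safety and leaves the IDMC to judge from incidence rates.

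**Working it through.** **Plan's own figures.** The documents give no bleeding rate, power or sample size, so there is no bleeding figure to reproduce. The only power calculation is for ischaemic stroke: 1,688 per group (protocol 11.1, SAP 4). It reproduces closely:

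- Schoenfeld events for a hazard ratio of 0.70: 4(1.96 + 0.842)² / (ln 0.70)² ≈ 247.
- Event probability with hazard λ, accrual A = 2.5 years and minimum follow-up F = 1 year: 1 − [exp(−λF) − exp(−λ(F+A))]/(λA). This is 0.0857 at λ = 0.04 and 0.0609 at λ = 0.028, with mean 0.0733.
- 247 / 0.0733 / 2 ≈ 1,685 per group.

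This has no bearing on bleeding.

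**Where a transfused bleed without haemodynamic compromise is counted**

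| Planned analysis | Included? | Identified as a group? |
|---|---|---|
| GUSTO severe or life-threatening (SAP 10.5) | No, unless intracranial | – |
| All haemorrhagic events (SAP 10.5) | Yes | No, mixed with minor bleeding |
| System organ class / preferred term (SAP 10.5) | Yes | No, split by term |
| Serious events and reactions (SAP 10.3, 10.4) | Only if serious | No, split by term |

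**Illustration 1, event counts.** Protocol 11.4.1 expects 8,000 person-years, so 4,000 per arm at 1:1. Assumed rates: severe 0.5%/year in both arms (20 vs 20 events); moderate 0.25 or 0.5%/year on SAPT, doubled on DAPT (10 vs 20, or 20 vs 40). The formulas are z = ln(E2/E1) / √(1/E1 + 1/E2) and power = Φ(z − 1.96), two-sided 5% as in SAP 6.5.

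| Comparison | Events | z | Power |
|---|---|---|---|
| Moderate alone, low rate | 10 vs 20 | 0.693/0.387 = 1.79 | 43% |
| Moderate alone, high rate | 20 vs 40 | 0.693/0.274 = 2.53 | 72% |
| Moderate or severe, low rate | 30 vs 40 | 0.288/0.242 = 1.19 | 22% |
| Moderate or severe, high rate | 40 vs 60 | 0.405/0.204 = 1.99 | 51% |
| Severe only | 20 vs 20 | 0 | no signal |

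**Illustration 2, dilution within all bleeding.** This uses patients with an event, 2,000 per group, and a two-sided 5% test of two proportions. Moderate bleeding doubles. All other bleeding is assumed equal in both groups, at 3 to 15%. The combined column assumes severe bleeding at 1% in both groups.

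| Moderate, SAPT vs DAPT | Moderate alone | Within all bleeding | Moderate or severe |
|---|---|---|---|
| 0.5% vs 1.0% | 45% | 6 to 13% | 23% |
| 0.75% vs 1.5% | 61% | 9 to 22% | 38% |
| 1.0% vs 2.0% | 74% | 13 to 33% | 53% |

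For example, with 3% other bleeding the first row compares 3.5% with 4.0%. The pooled standard error is √(2 × 0.0375 × 0.9625 / 2,000) = 0.0060, so z = 0.005/0.0060 = 0.83 and power is about 13%.

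Both illustrations give the same order for a moderate-only rise: the grade shown alone is most sensitive and the combined class less so. Illustration 2 puts all bleeding lowest, and the severe class contains none of the signal.

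**The case against.** The strongest reply is that these bleeds are not out of sight, and much of it stands. SAP 10.5 tests haemorrhagic events by preferred term, so gastrointestinal bleeding is compared apart from nosebleeds. SAP 10.3 and 10.4 do the same for serious events and reactions. Since hospitalisation makes an event serious under protocol 7.1.2, many transfused bleeds would probably appear there. What is missing is a row that gathers them by grade.

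A reader might infer that a rise in major extracranial bleeding as a whole could go unanalysed. The documents do not support that: extracranial bleeding with substantial haemodynamic compromise is in the severe class and is compared.

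A reader might also expect the combined class alone to bring high power. If one rate ratio of 2 applied to both grades, it would: 30 vs 60 events gives 87% and 40 vs 80 gives 95%. But under that assumption the severe-only test already has about 72% (20 vs 40). It is not the situation in which the planned analysis fails. When only the moderate grade doubles, the combined class gives 22 to 51%, which is why each grade must also be shown separately.

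Protocol and SAP agree on the named endpoint, so this is a gap and not a contradiction. Finally, protocol 24.7 does not mention transfusion, and the CRF manual, interim analysis protocol and IDMC procedure manual are not shown. Whether the grade can be derived, and what the IDMC tables already contain, cannot be confirmed.

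**Conclusion.** The point holds in a limited form. SAP 10.5 defines a transfusion-based grade and makes no pooled comparison of it, so a rise confined to that grade can be diluted in all bleeding or scattered over preferred terms. It would not show in the severe-only comparison.

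On the assumed rates, a doubling of moderate bleeding is detected with about 43 to 72% power when the grade is shown alone. It is detected with about 22 to 51% in the combined class, and 6 to 33% through all bleeding in the second illustration. Every bleeding rate here is an assumption, and the figures show direction and rough size only. Even the grade shown alone is only moderately powered, so the gain is mainly in visibility. The matter is minor: an inexpensive improvement to safety reporting that does not touch the primary analysis or the named safety endpoint.

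**What to change.** Add to SAP 10.5 that incidence will be given by treatment group for each GUSTO grade (severe or life-threatening, moderate, minor) and for moderate-or-severe combined. Count each patient at the highest grade reached and use the chi-square comparison already planned. Put the same rows into the by-treatment haemorrhagic-event tables for the IDMC. Keep severe or life-threatening haemorrhage as the named safety endpoint.

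Before this is adopted, the data center should confirm that transfusion can be identified from the adverse-event treatment entries; if it cannot, a specific item would have to be collected.

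The cost is one or two SAP sentences, a few table rows and a few more unadjusted safety comparisons. SAP 6.6 already makes no multiplicity adjustment for safety endpoints. Nothing in patient management changes.

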#### **GUSTO bleeding criteria**

-Severe or life-threatening hemorrhage:

Intracranial bleeding or bleeding that causes substantial hemodynamic compromise requiring treatment

-Moderate bleeding: Bleeding which requires blood transfusion

-Minor bleeding: Other bleeding, neither requiring transfusion nor causing hemodynamic compromise

### **10.6 Blood pressure**

Descriptive statistics will be calculated for the blood pressure (systolic, diastolic) values for each treatment group and timepoint and for the difference from the observation start date.

A figure will be prepared showing the change in the mean and standard deviation over time for each treatment group and value at each timepoint.

## 10.7 Other safety endpoints

### Degree of independence in activities of daily living (mRS)

Evaluate as one of following 7 levels according to Japanese Modified Rankin Scale (Japanese Guidelines for Management of Stroke 2009). A frequency distribution will be determined for each treatment group and timepoint, and a shift table will be prepared for the values at each timepoint before and after the start of the observation for each treatment group.

0. No symptoms at all
1. No significant disability despite symptoms: able to carry out all usual duties and activities
2. Slight disability: unable to carry out all previous activities, but able to look after own affairs without assistance
3. Moderate disability: requiring some help, but able to walk without assistance
4. Moderate to severe disability: unable to walk without assistance and unable to attend to own bodily needs without assistance
5. Severe disability: bedridden, incontinent and requiring constant nursing care and attention
6. Dead

**12. REVISION HISTORY**

| Version No. | Date              | Prepared by                    | Revision                                            |
|-------------|-------------------|--------------------------------|-----------------------------------------------------|
| 0.10        | January 24, 2014  | EPS
[name] | First version prepared                              |
| 0.20        | February 10, 2014 | EPS
[name] | Revised according to findings of January 30 meeting |
| 0.30        | February 18, 2014 | EPS
[name] | Revised according to February 13 findings           |
| 1.00        | March 10, 2014    | EPS
[name] | First version finalized                             |
